## Abstract

**Background:**

Although major depression is a frequent disorder in non-professional caregivers and there are effective psychological interventions to prevent it, caregivers have difficulty accessing them. Interventions for depression applied through an app could improve accessibility; yet, to date, adherence to such interventions has been low. The objectives of this study are to (1) evaluate the efficacy of a cognitive behavioral depression prevention intervention administered through a smartphone app with and without telephone conference calls, (2) analyze the mediators of the change in the incidence of depression and depressive symptoms, and (3) assess adherence and satisfaction with the interventions.

**Methods:**

A randomized controlled clinical trial will be conducted. Caregivers with elevated symptoms will be randomly assigned to a cognitive behavioral intervention administered by a smartphone app (CBIA) group, a CBIA plus telephone conference calls (TCCs) group (CBIA + TCC), or an attention control group. Each condition will consist of approximately 58 participants. Both interventions will be administered in five modules through a smartphone app and the CBIA + TCC group will receive additional TCCs in group format (four sessions of 30 min each). Trained blind assessors will conduct pre-treatment, post-treatment and follow-up assessments at 1, 3, 6, and 12 months.

**Discussion:**

This study will provide evidence of the efficacy of a cognitive behavioral intervention to prevent depression in caregivers with elevated depressive symptoms administered through a smartphone app and the impact of feedback applied through conference calls to increase program adherence and efficacy. If the results were favorable, it would mean that we have developed a more effective, accessible, and clinically useful preventive depression intervention than the currently available ones for many present and future caregivers.

**Trial registration:**

ClinicalTrials.gov: NCT03110991. Registered 5 April 2017.

**Electronic supplementary material:**

The online version of this article (10.1186/s13063-018-2793-2) contains supplementary material, which is available to authorized users.

## Background

In European countries, apprximately 54.5 million people are caregivers of a loved one in a situation of dependency [1]. However, staying in this situation for a prolongued period can affect their physical and mental health [2]. In the context of mental health, major depression is the most frequent mental disorder in this population, with a prevalence of 8.9% [3]. These figures are highly relevant because depression is associated with impaired function [4] and may interfere with the quality of care of the dependent [5].

Interventions to prevent depression may prevent or reduce the occurrence of these cases of depression. Specifically, prevention interventions aimed at caregivers with high depressive symptoms but who have not yet developed clinical depression (i.e., indicated prevention) have the greatest empirical evidence to date [6–9]. One of these interventions, evaluated by Vázquez et al. [8, 9], was developed based on Lewinsohn et al.’s [10] multifactorial integrator model of depression. This intervention found a significant reduction in the incidence of depression and depressive symptoms in the cognitive behavioral intervention group compared to the usual care control group at post-treatment [8] and after 12 months of follow-up [9]. Moreover, the changes found in relation to depressive symptoms were clinically significant [11]. Although these results are promising, the intervention was applied face-to-face, which may limit its impact on public health since this format presents a series of barriers that make it less accessible to caregivers. Many caregivers find it difficult to attend interventions due to lack of time, displacement problems, not having a caregiver substitute for their dependent during their absence, lack of mental health services, or stigmatization.

These accessibility issues could be easily mitigated through information and communication technologies, among which that with the greatest potential is the mobile phone. Mobile phones are owned by more than 80% of the world’s population [12], they are portable and can serve as a platform for a variety of apps thanks to its accessibility to programming and internet access (smartphones). However, there are currently only two randomized controlled trials that have evaluated interventions for the treatment of depression through an app, neither of which was aimed at preventing depression in caregivers and only showing partial improvements in the reduction of depressive symptoms. More specifically, Arean et al. [13] found no significant difference at the post-treatment and 1-month follow-up between a cognitive training intervention, another intervention based on problem-solving therapy, and an attention control group where participants received therapeutically inactive information on health (Health Tips). At the 3-month follow-up, participants in both interventions showed higher remission rates compared to controls (50% and 49% vs. 32%), but only those with moderate depressive symptomatology in the problem-solving therapy group showed less depressive symptoms than the control group (*d* = 0.76). In addition, Ly et al. [14] did not find any post-treatment differences between a program based on behavioral activation and another based on mindfulness. At the 6-month follow-up, the behavioral activation intervention was more effective for patients with greater initial severity of depression (*d* = 0.47), whereas the mindfulness intervention was more effective for patients with less severity (*d* = 0.98).

The limitations in both studies included problems of adherence to the interventions. Dropout rates were high, ranging from 14.8% [14] to 31.6% [13]; in the study by Arean et al. [13], 57.9% did not even download the assigned intervention app and the level of compliance with homework assignments was not reported. These issues are fundamental because individuals who leave the intervention show worse results and less satisfaction with the therapy, and when evaluating the efficacy of interventions, high dropout rates can lead to bias due to attrition, limiting the generalizability of the results [15]. In addition, homework completion is a significant predictor of therapy outcomes in various populations and interventions [16], including depression prevention interventions in the caregiver population [17]. This shows that when more homework is completed, the therapy results are better, leading to a greater reduction of depressive symptoms [17]. Complementing the interventions implemented through smartphones with a telephone conference call (TCC) to give feedback could help solve these problems. In behavioral skills training procedures, feedback is specifically defined as delivery of praise for correct performance of a target behavior and further instruction following incorrect performance [18].

The objectives of the present study are to (1) assess the efficacy of a cognitive behavioral intervention for indicated prevention of depression in informal caregivers, administered through a smartphone app (CBIA) with and without TCCs with respect to a care control group, (2) analyze the mediators of change in depressive symptoms, and (3) assess adherence and satisfaction with the interventions. As a central hypothesis, both interventions are expected to significantly reduce the incidence of depressive episodes and depressive symptoms compared to the control group at post-treatment and at 1-, 3-, 6-, and 12-month follow-up. Secondary hypotheses are (1) that the change in reinforcement and in negative automatic thoughts will mediate the effects of both interventions and (2) that the participants receiving CBIA + TCC will show greater adherence and satisfaction with the intervention than those who receive CBIA alone.

## Methods

### Design

A randomized controlled clinical trial will be conducted to study the efficacy of a cognitive behavioral intervention for non-professional caregivers with elevated depressive symptoms administered through a smartphone app with and without TCCs. Specifically, eligible participants will be randomly assigned to one of three conditions, as follows: (1) CBIA; (2) CBIA + TCC; and (3) an attention control group (ACG).

The study phases are shown in Fig. 1. There will be six measurement points in the three groups (i.e., pre-treatment, post-treatment, and follow-up at 1, 3, 6, and 12 months). After the baseline assessment (pre-treatment), and once caregivers who meet the eligibility criteria are selected and interventions are administered, a post-treatment evaluation and four follow-ups will be performed (at 1, 3, 6, and 12 months). To minimize the loss of participants, we will follow the strategies recommended by Grady et al. [19], such as selecting participants who are likely to adhere to the intervention, obtaining various means to contact the participants (address, telephone, email), and making the intervention easy.

**Fig. 1 Fig1:**
[figure not shown]
SPIRIT Figure. Phases of the randomized controlled trial. Note: * During the intervention and at post-treatment

### Sample size

Based on a previous study of indicated prevention of depression in caregivers [9], which involved the same program that will be evaluated in the present study (albeit in person), we estimate that a sample size of 49 participants per group (98 in total) would be sufficient to detect an 18.6% difference in the incidence rates of major depression episodes between the experimental group and the control, assuming a two-tailed test α of 0.05 and a power (1 – β) of 0.80. However, considering an attrition rate of approximately 15% based on studies that have evaluated the use of interventions for the treatment of depression applied through an app [14], we estimate that the number of participants per group should be 58, resulting in a final sample size of 174.

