### Statistical analyses

We will use the statistical package SPSS for Windows (version 21.0) for the analysis of the data. All analyses will be performed according to the intent-to-treat principle. If participants drop out from the study, the lost values ​​will be imputed using multiple imputation [33].

To analyze the incidence of depressive episodes in each of the measurement times (post-treatment, 1, 3, 6, and 12 months of follow-up), a global χ^2^ test will be performed to compare the three groups. If the differences are statistically significant (*p* < 0.05), pairwise comparisons will be performed using logistic regression. The relative risk and the required number of patients to be treated will be calculated following the formulas proposed by Guyatt et al. [34]. In addition, the time it will take participants to undergo a major depressive episode will be analyzed using a survival analysis. The analysis of the effect of the interventions on the outcome variable ‘depressive symptoms’ will be performed using two-way ANOVA with repeated measures. The analyses related to the effects of moderation or mediation will be carried out as per the recommendations of Baron and Kenny [35]. The model to evaluate moderation will include, as an independent variable, the type of treatment, the moderating potential, and the interaction between the two. An optimal combined moderator will also be sought according to Kraemer’s recommendations [36]. For the analysis of the mediation, we will perform adjustment of three regression equations to assess the effect (1) of the predictor variable (amount of treatment) on the dependent variable (change in depressive symptomatology after the intervention), (2) of the predictor variable in the mediator potential of the predictor variable (change in reinforcement and negative thoughts), and (3) of the mediator potential of the dependent variable, controlled by the predictor variable. Dropouts and adherence to interventions will be analyzed using a χ^2^ test to compare the percentage of dropouts and using an independent *t* test to compare the number of modules completed and the register of the intersessional tasks. Likewise, the level of satisfaction with the interventions will be assessed using the CSQ-8 through a frequency analysis and descriptive statistics, and both active conditions will be compared at post-treatment using an independent *t* test.

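### The stated 80% power covers one two-group comparison at unstated incidence rates; power for both active arms is not given, and it falls sharply if the pairwise logistic regressions are tested by Wald

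*Protocol article*

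**What the plan says.** The Sample size section (Protocol article) states: "we estimate that a sample size of 49 participants per group (98 in total) would be sufficient to detect an 18.6% difference". The total of 98 means two groups: one experimental arm against control. The test is two-sided at 0.05 with 80% power. The number is raised to 58 per group for about 15% attrition and applied to three groups, 174 in all. Neither the control nor the active incidence is stated.

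Under Statistical analyses, incidence at each time point is first compared across the three groups by a global chi-square test. If p < 0.05, "pairwise comparisons will be performed using logistic regression". Analyses are by intention to treat with multiple imputation of lost values. The test statistic within the logistic regression is not named.

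The Background gives the central hypothesis: "both interventions are expected to significantly reduce the incidence of depressive episodes and depressive symptoms compared to the control group".

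**The concern.** The 80% describes one unadjusted comparison of two proportions. It does not describe the sequence that will be run, or the hypothesis that both active arms beat control.

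The event counts add a second problem. A sample of 49 per group for a difference of 18.6 points is possible only if the active-arm incidence is very low. The Wald test of a log odds ratio is weak when one arm has one or two events, and it fails when an arm has none. If the pairwise comparisons are read from Wald p-values, an intervention that works as assumed could be reported as non-significant on the primary outcome because of the test.

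**Working it through.** **1. The plan's own arithmetic.** 49 / 0.85 = 57.6, rounded up to 58; 3 × 58 = 174. This reproduces. The figure 49 cannot be recomputed directly because the rates are missing, but it can be solved for them. Let p be the active rate, p + 0.186 the control rate, z(0.975) = 1.960 and z(0.80) = 0.842.

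- Unpooled: n = (1.960 + 0.842)² × [p(1 − p) + (p + 0.186)(0.814 − p)] / 0.186². At p = 0.0418: 7.849 × (0.0401 + 0.1759) / 0.0346 = 49.0. Rates about 4.2% vs 22.8%.
- Pooled variance under the null: n = 49 at about 3.4% vs 22.0%.
- Arcsine: n = 49 at about 4.9% vs 23.5%.
- Pooled with continuity correction: n = 49 at about 0.2–0.5% vs 18.8–19.1%.

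Under the first three, the expected count in an active arm of 49 is 1.7 to 2.4 events.

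**2. Power of the planned sequence.** All combinations of three binomial counts were enumerated exactly, with both active arms at the full 18.6-point effect. The rule applied was a 2-df Pearson chi-square at 0.05, then each pairwise test at two-sided 0.05. Under Wald, a zero-event arm counts as not significant. The analysed number is 49 (completers only) or 58 (no information lost to imputation, an upper bound). The data are treated as complete; pooling over imputations is not modelled.

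| Active vs control | Pairwise test | 49: one comparison | 49: both | 58: one comparison | 58: both |
|---|---|---|---|---|---|
| 3.4% vs 22.0% | Wald | 60.6% | 44.8% | 72.6% | 57.9% |
| | Likelihood-ratio | 83.5% | 77.5% | 89.8% | 85.6% |
| | Pearson | 83.5% | 77.5% | 88.8% | 83.7% |
| 4.2% vs 22.8% | Wald | 64.2% | 50.2% | 75.5% | 63.0% |
| | Likelihood-ratio | 80.1% | 73.4% | 87.2% | 82.3% |
| | Pearson | 80.1% | 73.4% | 86.1% | 80.1% |
| 4.9% vs 23.5% | Wald | 65.6% | 52.7% | 76.5% | 65.3% |
| | Likelihood-ratio | 77.3% | 70.1% | 84.9% | 79.4% |
| | Pearson | 77.3% | 70.1% | 83.8% | 77.3% |

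**3. Where the loss arises** (4.2% vs 22.8%, 49 per arm). Without the gate, one comparison has 83.2% power by likelihood-ratio and 65.2% by Wald, so the test accounts for 18 points. Adding the gate gives 80.1% and 64.2%, a cost of 3.1 and 1.0 points. Requiring both comparisons gives 73.4% and 50.2%, a further 6.7 and 14.0 points. Over the three sets of rates, the gate costs 0.6 to 3.6 points per comparison.

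**4. Zero-event arms.** At 4.2%, P(no events in 49) = 0.958^49 = 12%. For at least one of the two active arms it is 1 − (1 − 0.122)² = 23%. With 0/49 vs 11/49, the Pearson p is 0.0004 and the likelihood-ratio p is below 0.001, but the logistic Wald p is about 0.998. The global test still sees the effect: for 0, 2 and 11 events in 49 each, chi-square is about 17.4 on 2 df (p < 0.001).

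**5. Number needed for 80% on both comparisons** (3.4% and 4.2% rates): 52–56 analysed per arm with likelihood-ratio, 74–78 with Wald.

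**The case against.** The strongest reply is that the low figures rest on choices the article does not make. It gives no rates and does not name Wald, and naming a test statistic is commonly left to the analysis plan. With a likelihood-ratio test, a single gated comparison stays at 77–84%, close to the stated 80%. If the 49 came from a continuity-corrected formula (about 0.5% vs 19%), Wald power would be about 15% per comparison and likelihood-ratio power about 97%. No single figure can be quoted without the rates and the test. This stands, and it is why the results are given as conditional ranges. It does not remove the point: multiple imputation followed by logistic regression ordinarily ends in pooled coefficients and standard errors, which is a Wald-type test. The article does not rule that out.

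Some readers may infer more than the documents support:

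- That the trial simply has about 65% or 50% power. Those values hold only for Wald, 49 analysed per arm and roughly 4% vs 23%.
- That the three-group gate is to blame. It costs at most about 3.6 points.
- That the trial fails unless both arms win. The Background states an expectation about both interventions, not a success rule, and sizing each active-vs-control comparison separately is a common choice.
- That a perfect result would be declared null. Only the Wald pairwise test fails there; the global chi-square does not, and a survival analysis is also planned.
- That the 15% attrition and the in-person source of the effect are errors. Both are disclosed assumptions. The Background cites app-trial dropout from 14.8% to 31.6%, but the Discussion reports 6.6% in a conference-call study.

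**Conclusion.** The point holds in a limited form. The 80% belongs to one two-group comparison whose rates are not stated, and no power is given for the hypothesis that both interventions work. At the rates implied by formulas without continuity correction and 49 analysed per arm, power for both is 70–78% with a likelihood-ratio or Pearson test and 45–53% with Wald. Per comparison it is 77–84% and 61–66%. At the upper bound of 58 per arm, power for both is 77–86% and 58–65%, so with a suitable test the shortfall is small or absent. The main causes are the Wald test with about two events per active arm and the need for two significant results. The sample-size arithmetic itself reproduces, and 174 need not change. The conclusion assumes the full effect in both active arms and complete-data tests.

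**What to change.** Keep 174 participants.

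- In Sample size, state the assumed control and active incidence and the formula used. Say that 80% applies to one active-vs-control comparison. Add the power for both arms at those rates; at the rates implied here it is about 70–78% with 49 per arm, to be replaced by the authors' own figure.
- In Statistical analyses, replace the default Wald test by a pairwise test that remains valid with sparse or zero cells and can be combined across imputations. Examples are a risk difference, Firth-penalised logistic regression with a penalised likelihood-ratio test, or a pooled chi-square. Name the combining method.
- Optionally add a sensitivity figure at 31.6% attrition. 58 × (1 − 0.316) = 39.7, about 40 per arm; at 4.2% vs 22.8%, power for both is about 62% with likelihood-ratio or Pearson and 32% with Wald.

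The cost is wording and analysis specification only. The stated power for the two-arm claim becomes somewhat less favourable, but the change of test recovers real power on the primary outcome if Wald would otherwise have been used.

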### Participants, recruitment, and eligibility criteria

Participants will be recruited from the population of non-professional caregivers of persons in a situation of dependency officially recognized by the Regional Government of Galicia. Galicia is a region in the northwest of Spain with an area of 29,434 km^2^ and a population of 2,730,337.

It has been previously determined that between 39% and 44% of caregivers present with elevated depressive symptoms [7, 8] and 8.9% have had a major depressive episode [3]. As a result, to achieve the estimated sample of about 174 participants, we would need to select approximately 532 caregivers for screening prior to verification of eligibility criteria.

Caregivers will be contacted through a letter inviting them to participate in the study and asking them to return a sealed postcard if they do not wish to be contacted again. Caregivers who do not send the card will be contacted by phone. At that time, a brief description of the study will be given, and those who are interested will receive a brief screening call to evaluate their depressive symptoms, the diagnostic criteria for major depressive episodes, and the eligibility criteria. Those who meet the initial selection criteria will be invited to participate in a full evaluation through the app.

To be included in the study, participants must meet the following inclusion criteria: (1) be a non-professional caregiver of a dependent family member whose dependency is officially recognized by the Regional Government of Galicia; (2) have a smartphone; (3) present a clinically significant symptomatology defined as a score equal to or greater than 16 in the Spanish version of the Center for Epidemiologic Studies Depression Scale (CES-D [20]); (4) not meet the diagnostic criteria for a major depressive episode according to the Diagnostic and Statistical Manual of Mental Disorders (DSM-5) [21]; (5) not have a history of major depression; (6) commit to participating in all evaluations; and (7) provide written informed consent. Participants who meet the following criteria will be excluded: (1) receiving psychological or psychopharmacological treatment in the last 2 months; (2) have other disorders that may act as confounding variables (e.g., symptoms due to substance use); (3) have severe psychological or medical disorders requiring immediate intervention (e.g., suicidal ideation) or that make the study impossible (e.g., significant cognitive impairment); (4) that the person in a situation of dependence has a severe or terminal prognosis within the next 14 months; or (5) that in the next 14 months they plan to move or to institutionalize the dependent they were caring for.

### Randomization

Those participants who meet the eligibility criteria will be randomly assigned to one of the three conditions, CBIA, CBIA + TCC, or ACG, by a statistics expert not related to the study using a table of random numbers generated by a computer. The sequence of randomization will be communicated to the researchers by means of sealed numbered envelopes, one for each participant, with instructions to use them in numerical order. Due to the nature of the intervention, it is not possible to blind the participants for allocation status.

